## Abstract

**Introduction:** Non-melanoma skin cancer (NMSC) incidence is increasing, and occupational solar exposure contributes greatly to the overall lifetime ultraviolet radiation (UVR) dose. This is reflected in an excess risk of NMSC showing up to three-fold increase in outdoor workers. Risk of NMSC can be reduced if appropriate measures to reduce UVR-exposure are taken. Regular use of sunscreens showed reduced risk of NMSC. However, sun-safety behavior in outdoor workers is poor. The objective of this study is to investigate the effectiveness of an intervention aiming at increasing sunscreen use by construction workers.

**Methods:** This non-randomized controlled intervention study is comprised of two intervention and two control groups recruited at four different construction sites in the Netherlands. The study population comprises ~200 construction workers, aged 18 years or older, followed during 12 weeks. The intervention consists of providing dispensers with sunscreens (SPF 50+) at construction sites and regular feedback on the application achieved by continuous electronic monitoring. All groups will receive basic information on UV-exposure and skin protection. Stratum corneum (SC) samples will be collected for measurement of biomarkers to assess internal UV-dose. External UV-dose will be assessed by personal UV-sensors worn by the workers during work-shifts in both groups. To detect presence of actinic keratosis (AK) or NMSC, a skin check of body parts exposed to the sun will be performed at the end of the study. The effect of the intervention will be assessed from data on self-reported sunscreen use by means of questionnaires collected on baseline and after 12 weeks of intervention (primary outcome). Levels of SC biomarkers of internal UV-dose, external UV-dose, number of sunburn episodes, and prevalence of NMSC including AK will be assessed as secondary outcomes. The electronically monitored sunscreen consumption will be assessed as process outcome.

**Discussion:** This study is intended to provide evidence of the effectiveness of a technology-driven intervention to increase sunscreen use in outdoor construction workers. Furthermore, it will increase insight in the UV-protective behavior, external and internal UV-exposure, and the prevalence of NMSC, including AK, in construction workers.

**Trial Registration:** The Netherlands Trial Register (NTR): NL8462 Registered on March 19, 2020.

## Introduction

Globally, non-melanoma skin cancers (NMSC) are the most common cancers in fair-skinned populations (1). Solar ultraviolet radiation (UVR) is the main cause of NMSC in fair-skinned people, responsible for ~50–70% of squamous cell carcinoma (SCC) and 50–90% of basal cell carcinoma (BCC) (2, 3). Recently, systematic reviews found that the risk among outdoor workers was raised for SCC and actinic keratosis (AK) by 77%, and for BCC by 43% respectively, compared with the general population (4, 5). Occupational solar exposure contributes greatly to the overall lifetime UV dose. This is reflected in an excess risk of NMSC showing up to three-fold increase in outdoor workers (6). High and increasing incidence rates and frequent recurrence have considerable impact on life and productivity of affected workers. This burden is recognized by the World Health Organization (WHO) and the International Labour Organization (ILO) in a recently published a protocol for a systematic review on the effect of occupational UVR-exposure on NMSC prevalence (7). In six EU countries NMSC has been recognized as an occupational disease (8). NMSC can largely be avoided if appropriate measures to reduce UVR are taken. Several prevention strategies have been developed based on educational programs or use of sunscreens and protective clothing such as long-sleeved shirts and wide-brimmed hats (9). Sunscreen is shown to be an efficient strategy to reduce UVR exposure and its consequences (10, 11). It is a feasible measure to adopt by outdoor workers (12–14), and when used regularly, sunscreens are able to prevent the formation of actinic keratosis and eventually squamous cell carcinoma (10, 11). However, previous research revealed several barriers to using sunscreen, such as the common belief that people with a tanned or dark skin are not at risk for skin cancer and protective measures are not necessary (10, 15), or that sunscreens are expensive (16). Also, generally positive attitudes toward a tanned skin are associated with a decrease in sunscreen use, preventing outdoor workers from taking sun protection seriously (10, 17). Putting on sunscreen is seen as a disturbance and a nuisance, for example it is messy and time-consuming to apply (10, 16, 17). Furthermore, many outdoor workers are male and they may feel it is not masculine to protect themselves from the sun (10, 18), especially around other men (10, 19). Sun-safety behavior among outdoor workers is still poor (10, 20, 21), with examples of 75% of operating engineers seldom or never using sunscreen and 80% of those workers reporting sunburns during the summer (10). However, in another study the majority of outdoor workers did use sunscreen during the summer but they used it incorrectly regarding time, frequency and amount applied (21). Additionally, a recently published meta-analysis showed that the most effective intervention for promoting sunscreen use is providing free sunscreen (22).

Several gaps in the current knowledge are to be filled, these are the prevalence of NMSC including AK, the occupational UV-exposure, and ultimately the effectiveness of an intervention aimed at increasing of sunscreen use in outdoor workers. Well-designed and sufficiently powered studies with adequate adjustment for confounding factors are required to provide more accurate risk estimates for occupational NMSC (23). Data on UV-exposure (external and internal, i.e., the UV-dose that reaches the surface of the skin and the UV-dose absorbed by the skin, respectively), presence of NMSC (including AK), and sunscreen use in outdoor workers in the Netherlands are not yet available.

### Objectives

The objectives of this study are (i) to evaluate an intervention consisting of the facilitation of sunscreen dispensers with continuous electronic monitoring and feedback on the use of sunscreens at worksites, and (ii) to assess occupational UV-exposure and the prevalence of NMSC, including AK, among construction workers.

### Hypothesis

We hypothesize that provision of sunscreen dispensers (facilitation), accompanied by continuous monitoring and intermittent feedback on sunscreen use (awareness and feedback), will significantly increase the use of sunscreen amongst construction workers compared to a control group.

## Methods/Design

### Design and Setting

This is a non-randomized controlled intervention study in construction workers. The duration is 12 weeks, from May to July. The measurements will consist of questionnaires, clinical and biochemical assessments, personal UV-dosimetry, and continuous electronic sunscreen consumption records. When reporting the results of this study we will adhere to the Transparent Reporting of Evaluations with Non-randomized Designs (TREND) statement (24).

A nationwide construction company in the Netherlands will appoint four comparable construction sites suitable for the study. Two sites will serve as the intervention groups and the other two construction sites will serve as the control groups. To minimize potential bias induced by non-randomization, the control groups will be matched to the intervention groups regarding worksites and job tasks, geographical location of the worksites, and time-frame. To avoid contamination bias, the whole construction site will be assigned en masse to the intervention group and there will be no rotation of workers between the four workplaces.

A process evaluation of the intervention will take place in the closing questionnaire to support a future implementation process.

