### Power Calculation

The study is planned to include 200 participants. The sample size is based on the expectation regarding the change in sunscreen usage. There is no available data on sunscreen use in outdoor workers in the Netherlands, or the barriers for sunscreen use. Therefore, we based our calculations of the sample size on a Canadian study reporting that 25% of the outdoor workers used sunscreen regularly (47). We assumed that 25% of the outdoor workers in the control groups will use sunscreen, and that in the intervention groups we expect this percentage will increase up to 50%. To calculate the sample size, nQuery Advisor software (Statistical Solutions Ltd, Boston, MA, U.S.A.) was used (proportion, two groups, two-sided test). A sample size of 58 workers per group will have 80% power to detect a difference in proportion that equals at least 0.05 significance level. Taking into account possible drop-outs, 100 outdoor workers per group will be recruited.

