### Statistical Methods and Data Analysis

There will be no replacement of any individual subjects who withdraw. However, the characteristics (e.g., job task, age) and number of withdrawals will be monitored.

The characteristics of the construction workers (e.g., age) and job tasks will be presented by using descriptive statistics. We will use the mean and standard deviation to describe normally distributed continuous variables and the median and interquartile range to describe non-normally distributed continuous variables. For the self-reported sunscreen usage data (primary outcome), counts and percentages to present categorical variables will be used. The self-reported sunscreen usage data will be dichotomized and analyzed by Chi-squared statistical test to establish whether sunscreen consumption will differ between the intervention and control groups. Two-sided *p*-values of <0.05 will be considered statistically significant and statistical uncertainty will be expressed using two-sided 95% confidence intervals. For the main study parameter, intention-to-treat analysis will be performed.

For the secondary study parameters we will present the levels of biomarkers and the number of sunburn episodes as quantitative, continuous variables. The biomarker levels at T = 6 weeks and T = 12 weeks will be compared with the baseline levels using paired ANOVA test followed by the correction for multiple testing, dependently on the distribution of data. The presence of NMSC including AK will be presented as counts and percentages.

UV-exposure measured by UV-dosimeters will be presented per job task, and as average of the measurements by all workers who worn the dosimeter in the same period. Data will be presented as average dose per day. Furthermore, the UV-exposure pattern during the work shift will be revealed.

The distribution will be tested by using Shapiro-Wilk normality test.

Before data analysis, a detailed data analysis plan will be available.

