A limitation of this study is the lack of randomization, which was not feasible. However, the intervention and control groups will be matched regarding same sample size, working environments, and job tasks. The risk of contamination bias is limited because the participants work on different and separated work sites, and therefore are not influenced by the other groups. However, we will give basic information on sun-safety and UV-protective behavior at the beginning of the study (baseline) in the control groups also, therefore this might lead to change in sun-protective behavior. Nevertheless, we cannot withhold basic information from the control groups for ethical reasons. The risk of recall bias cannot be entirely avoided because we use questionnaires to measure the primary outcome, however, we counteract by limiting the timeframe through asking questions concerning 1 month in the past. Lastly, it is known that the body location of the UV-dosimeter has an impact on the measured exposure (52). However, we use UV-dosimetry only on one body location (i.e., the upper left arm) because this is practicable for construction workers, and this is the same body location as a large European study (27) used which makes comparison of UV-exposure between our studies and other countries more feasible.

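### The primary test does not use the site matching that is the plan's stated safeguard, so it is biased if the arms are split differently over matched sites that also differ in usual sunscreen use.

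*Protocol article*

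**What the plan says.** **Design.** Under Design and Setting, "Two sites will serve as the intervention groups and the other two construction sites will serve as the control groups". The same section offers matching as the means of limiting bias from the lack of randomisation: "the control groups will be matched to the intervention groups regarding worksites and job tasks, geographical location of the worksites, and time-frame". The Discussion repeats this as the answer to the study's main acknowledged limitation: "the intervention and control groups will be matched regarding same sample size, working environments, and job tasks".

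**Primary analysis.** Statistical Methods and Data Analysis fixes the test: "The self-reported sunscreen usage data will be dichotomized and analyzed by Chi-squared statistical test", comparing the intervention groups with the control groups, with "Two-sided *p*-values of <0.05 will be considered statistically significant". It names no matched pair, site or covariate term. It also says that withdrawals will not be replaced and that a detailed analysis plan will be available before the data are analysed.

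**Sample size.** Power Calculation treats the arms as two independent proportions. It takes 25% use in the control groups and 50% in the intervention groups, needs 58 workers per arm and recruits 100 per arm to allow for drop-out. No site size is given anywhere.

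**The concern.** Matching makes two arms comparable in a pooled table only if each arm draws its answers from the matched sites in the same proportions. Otherwise the pooled rate in each arm is a different weighted average of the site rates. Any difference in usual use between sites then enters the estimated effect.

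The plan does not secure equal proportions. Participation is voluntary, losses are not replaced, and the margin from 58 needed to 100 recruited leaves room for considerable loss. The primary p-value and risk difference could therefore depend partly on who answers at which site. The matching described in the design offers a way to remove that dependence, and the stated test does not use it.

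**Working it through.** **1. The plan's own figure.** Inputs from Power Calculation: 25% and 50%, two-sided 0.05, power 80%. With mean proportion 0.375:

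n = [1.960 × √(2 × 0.375 × 0.625) + 0.842 × √(0.25 × 0.75 + 0.50 × 0.50)]² / 0.25² = (1.342 + 0.557)² / 0.0625 = 57.7, so 58 per arm.

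This reproduces the stated 58. Power at 100 per arm is 96%. The calculation has no matching or site term, in line with the stated test.

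**2. Formula for the bias.** Let A and B be the matched pairs, with usual use pA and pB. Let wI and wC be the shares of the intervention and control answers that come from pair A. With no true effect,

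pooled difference = (wI − wC) × (pA − pB).

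The product is zero if either factor is zero. Both conditions are therefore needed.

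**3. Only one condition present** (100 per arm; rates and splits assumed).
- Same split in both arms (70/30 vs 70/30), with pair rates of 20/30%, 15/35% or 10/40%: bias 0, pooled rejection 3.6% to 4.9%.
- Different splits (70/30 vs 30/70), same use in both pairs (25%): bias 0, rejection about 5%.

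**4. Both conditions present, no true effect** (100 per arm, both sites of a pair given the same rate). Rejection rates are from simulation.

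| Use in pairs A/B | Answers A/B, intervention vs control | Pooled rates | Spurious difference | Pooled test rejects | Pair-stratified test rejects |
|---|---|---|---|---|---|
| 25/30% | 60/40 vs 40/60 | 27% vs 28% | 1 point | 5.3% | about 5% |
| 20/40% | 55/45 vs 45/55 | 29% vs 31% | 2 points | 5.7% | about 5% |
| 20/40% | 60/40 vs 40/60 | 28% vs 32% | 4 points | 9% | about 5% |
| 20/40% | 65/35 vs 35/65 | 27% vs 33% | 6 points | 15% | about 5% |

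Worked example, last row: (0.20 × 65 + 0.40 × 35)/100 = 0.27 and (0.20 × 35 + 0.40 × 65)/100 = 0.33. By the formula, (0.65 − 0.35) × (0.20 − 0.40) = −0.06. Exchanging the arms reverses the sign.

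Loss at one site only does less. With 20/40% use and one control site falling from 50 answers to 29 (a 42% loss), the bias is 2.7 points and pooled rejection is about 6.4%.

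**5. A true effect.** Assume 15/35% usual use, a true gain of 25 points in each pair, and 65/35 vs 35/65 answers. The pooled rates are 47% and 28%, so the difference shrinks to 19 points. Power is 80% pooled and 95% stratified.

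**6. What stratifying does not do.** Add an assumed intra-site correlation of 0.02 to the 20/40% setting with no true effect. At 60/40 vs 40/60 the pooled test rejects about 20% and the stratified test about 16%. At 50/50 in both arms the figures are about 15.6% and 16.6%. Both tests exceed 5%, and with balanced splits stratifying brings no gain in error rate.

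**The case against.** **Unequal pair sizes.** A reader might infer that pairs of unequal size are enough to create or hide an effect. Step 3 shows otherwise: a large pair and a small pair do no harm if both arms have the same split.

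**Pairing is not documented.** The article speaks of control groups matched to intervention groups and of four comparable sites. It never links a particular control site to a particular intervention site. Arm-level matching fits the wording too. This stands: one-to-one pairing is an inference from two sites against two, matched on location and tasks. It is why the fix begins by asking for the pairs to be named.

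**Equal sample size is planned.** The Discussion includes it among the matched features, and under balance the pooled test is at most slightly conservative. But that sentence refers to the groups and gives no site sizes. It does not secure equal numbers of 12-week answers at each site. Equally, the drop-out allowance is a per-arm figure and is no evidence that loss will differ between sites.

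**The larger figures rest on unfavourable inputs.** A gap of 20 points in usual use, with mirror-image splits, is a strong assumption for comparable sites of one company over one May-to-July window. This stands, and the milder rows belong beside the larger ones.

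**A later analysis plan is announced.** It could add the stratum. The article nevertheless commits to a named test without one, so the point concerns what is fixed, not what is left open.

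**Conclusion.** The concern holds in a conditional form. The plan relies on matching against non-randomisation bias and then fixes a primary test that does not condition on it. The pooled comparison is biased only when the arms are split differently over the matched sites and those sites also differ in usual use. The direction depends on which arm has more answers from the higher-use pair.

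Under the assumptions in the table, the cost under no true effect runs from negligible (5.3% to 5.7% rejection) to material (9% with 4 points, 15% with 6 points). No site sizes or site rates are documented, so none of these is a forecast.

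A reader might also infer that a pair-stratified test secures the nominal 5%. The documents do not support that. The figure assumes no site effect beyond the pair, and with an assumed intra-site correlation of 0.02 both tests reject about 16% or more.

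**What to change.** Before recruitment, which the article says had not started at submission:

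1. State which control site is matched to which intervention site. If no such pairing is intended, say so and say at what level the matching is done.
2. Stratify the primary comparison by matched pair, using a Mantel-Haenszel risk difference and test, or pair as a fixed factor in whatever model is used.
3. Report both pair-specific differences beside the combined one, with the number of 12-week answers at each site.

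The cost is analysis wording; no further data or participants are needed. Power at 100 per arm is about 96% for either test with balanced splits. If splits are very unequal and the pairs turn out not to differ (25% use in both, 70/30 vs 30/70), stratifying lowers power from 96% to about 93%. Within-site correlation has to be dealt with separately.

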### Participants and Recruitment

The participants in this study are construction workers, engaged in outdoor work activities. The participants are aged 18 years or older, have expressed the willingness to comply with the study protocol, and provided informed consent (inclusion criteria). The construction workers will be recruited by the occupational health service of their company. The construction workers will receive a letter from the investigators stating the purpose of the study, a short version of the study protocol, and a brief description of the expected burden for the participant during the intervention. Information regarding the intervention will be omitted for the participants in the control groups. The participants will be advised to contact the independent physician if they have additional questions regarding health risk associated with the study. The participants will be asked for their consent by the investigator and sign an informed consent form. The participants will have at least 24 h to consider their decision.

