### Blinding

Due to the study design and the placement of dispensers on the intervention work sites, it is not possible to blind the participants and investigators. The analysis of the SC samples will be performed blinded, the samples will be coded and the unblinding will be performed after all data are analyzed and archived in the laboratory.

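### Workers at intervention sites consent knowing of the intervention and control workers do not, which opens the primary comparison to differential recruitment that the stated analysis does not address

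*Protocol article*

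**What the plan says.** Under Design and Setting, "A nationwide construction company in the Netherlands will appoint four comparable construction sites suitable for the study". Two sites become intervention sites and two become control sites, without randomisation, and "the whole construction site will be assigned en masse to the intervention group". Control sites are "matched to the intervention groups regarding worksites and job tasks, geographical location of the worksites, and time-frame". The Discussion adds sample size and working environment to the matching.

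Under Participants and Recruitment, workers receive a letter that explains why the study is done and gives them "a short version of the study protocol, and a brief description of the expected burden for the participant during the intervention". Then comes the sentence at issue: "Information regarding the intervention will be omitted for the participants in the control groups". Eligible workers are adults who "have expressed the willingness to comply with the study protocol, and provided informed consent (inclusion criteria"). The section on study procedures adds that the investigator informs workers orally as well as in writing before consent. Under Blinding, "it is not possible to blind the participants and investigators".

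The primary outcome is self-reported frequency of sunscreen use over the last month, compared between arms. It is dichotomised and tested with a chi-squared test on an intention-to-treat basis. The same topic is asked at T = 0 and T = 12 weeks, but the stated test does not bring in the T = 0 answer.

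**The concern.** A worker enters this study only by agreeing to it, and what he is asked to agree to depends on his site. At intervention sites the description includes a sunscreen intervention; at control sites that part is left out. The information that differs concerns the behaviour that the primary outcome measures. The Introduction itself reports that many outdoor workers find sunscreen messy, time-consuming or unmasculine. Such workers might decline a study presented with sunscreen dispensers and monitoring more readily than one presented as measurements only.

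If consent depends on sunscreen habits in one arm and not in the other, or in a different way, the enrolled arms differ in use from the start. An unadjusted comparison at 12 weeks would count that difference as an intervention effect. Intention-to-treat does not help, because it preserves the groups as enrolled, including any imbalance. A larger sample does not help either: a fixed gap between arms is rejected more often as the number per arm grows.

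**Working it through.** **Which safeguards reach the problem**

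- Matching is on worksite, job task, location, time-frame, sample size and working environment. Prior sunscreen use, attitude and skin type are not among these. Even perfectly matched sites can yield different volunteers if the volunteers are told different things.
- The primary test compares dichotomised use between arms. No baseline adjustment is stated.
- The limitations in the Discussion name non-randomisation, contamination, the basic information given to controls, recall bias and dosimeter position. Differential recruitment is not named.

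**The plan's own figure**

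Inputs from Power Calculation: 25% use in control, 50% in intervention, two-sided 0.05, 80% power. With mean proportion 0.375:

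n = [1.960 × √(2 × 0.375 × 0.625) + 0.842 × √(0.25 × 0.75 + 0.50 × 0.50)]² / 0.25² = (1.342 + 0.557)² / 0.0625 ≈ 57.7, so 58 per group.

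The stated 58 is reproduced (power 80.2%, no continuity correction). The sample size is not in question; the formula serves below to show what selection alone could do.

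**Illustration of size**

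Assumptions, none of which the documents give except the 25%: true use is 25% at all four sites; consent at control sites does not depend on use; at intervention sites a share *u* of users and *v* of non-users consent; the intervention has no effect and use stays as it was at entry; workers are independent.

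Share of users among those enrolled at intervention sites: p = 0.25u / (0.25u + 0.75v).

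- u = 0.55, v = 0.50: 0.1375 / (0.1375 + 0.375) = 0.268
- u = 0.60, v = 0.50: 0.150 / (0.150 + 0.375) = 0.286
- u = 0.65, v = 0.45: 0.1625 / (0.1625 + 0.3375) = 0.325

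Probability that the uncorrected chi-squared test of p against 0.25 gives a two-sided p-value below 0.05, by exact enumeration of both binomial counts:

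| Users / non-users consenting | Enrolled users, intervention vs control | 58 per arm | 100 per arm |
|---|---|---|---|
| 55% / 50% | 26.8% vs 25% | about 6% | about 6% |
| 60% / 50% | 28.6% vs 25% | 7% | 9% |
| 65% / 45% | 32.5% vs 25% | 15% | 22% |

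Check of the last row by normal approximation at 100 per arm: mean proportion 0.2875; null standard error √(0.2875 × 0.7125 × 2/100) = 0.0640; alternative standard error √((0.1875 + 0.2194)/100) = 0.0638; (0.075 − 1.960 × 0.0640)/0.0638 = −0.79, giving 0.214, plus 0.001 in the other tail, or 0.215. Exact enumeration gives 21.7%, of which 21.6 points favour the intervention.

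The 58 is the number the power calculation needs and the 100 is the number recruited before drop-out, so the analysed number probably lies between them.

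**The case against.** The strongest case on the other side has five parts.

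1. *The incentive is not documented.* Dispensers stand in canteens and offices and the whole site is assigned. Nothing described restricts the sunscreen to enrolled workers, so consent need not be the price of using it. This weakens the mechanism but does not remove it, because how a study is presented can still affect who agrees to join.

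2. *The direction is open.* A reader might infer that the bias must run towards the hypothesis. The documents do not support that. Habitual users may see no need for a dispenser, workers deterred by the cost of sunscreen may be the ones attracted, and others may dislike monitoring. Control workers are told the study purpose and are offered a sun-safety talk and a skin check, which may also draw sun-conscious volunteers. If they too were selected, at 60% of users and 50% of non-users, against 65% and 45% at intervention sites, rejection would fall to roughly 7% at 58 and 9% at 100 per arm. This objection stands.

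3. *The baseline answer is available.* Use, attitudes and barriers are asked at T = 0, and a detailed analysis plan is promised that may adjust for them. A reader might also infer that the baseline answers are already distorted by knowledge of the dispensers. The article does not date the disclosure or the installation relative to T = 0. The item concerns the past month, so if dispensers are not yet in use, knowing of them can change only the reporting. What remains is that the primary test as stated does not use the T = 0 answer.

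4. *Withholding details from controls has a purpose.* It plausibly limits contamination and reactive behaviour. That is a good reason to keep controls uninformed. It does not require intervention-site workers to be informed before they consent.

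5. *Non-randomisation is declared.* The Discussion states: "A limitation of this study is the lack of randomization, which was not feasible". A reader might conclude that drawing lots within matched pairs would settle the matter. It would not: randomised sites with unequal letters keep the same selection. The article gives no reason for infeasibility, but nothing in it shows that the statement is wrong. That is a separate question.

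**Conclusion.** The point holds as a risk built into the recruitment procedure. It is certain from the text that the arms receive different information before consent and that consent governs entry. It is also certain that neither the site matching nor the stated primary test corrects for selection within a site, and that the limitations do not list it.

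It is not established that the arms will in fact differ, by how much, or in which direction. Enrichment of the intervention arm with sunscreen users is plausible and no more. Under the assumed consent rates the false-positive rate ranges from about 6%, close to nominal, to 15% at 58 and 22% at 100 per arm. The upper figures rest on a 20-point difference in consent at intervention sites and none at control sites, and should not be read as an estimate. The change is worth making because it is cheap before recruitment starts, while unequal recruitment cannot be undone after enrolment.

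**What to change.** - Use the same neutral letter and the same oral information at all four sites, without dispenser details.
- Obtain consent and the completed T = 0 questionnaire before dispenser details are disclosed at any site.
- Then give intervention-site workers those details in an information addendum, subject to approval by the ethics committee.
- Report the number approached and the number consenting at each site.
- Adjust the primary comparison for the T = 0 sunscreen-use answer, and name differential recruitment among the limitations.

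This keeps control workers uninformed of the dispensers, as now planned. The cost is a revised letter, an addendum and an ethics amendment, and the drawback is that intervention-site workers learn of the intervention in two stages, which the committee has to accept. The T = 0 answer is already collected, so the adjustment needs no new data. The article states that recruitment had not started at submission; if it has started since, the participation report and the adjustment remain possible, but equal recruitment information does not.
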